#### **4. Aims and issues of the project**

##### **Primary outcome**

- Rate of incorrect medication administration will be compared between control and intervention group at 6-month follow-up.

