## **11. Study procedure**

The study will be carried out in community pharmacies with which other projects have already established cooperation. Prior to the start of the study, pharmacy staff will be informed of erroneous and correct administration of the different dosage forms (see inclusion criteria) known from the literature, the use of study materials, and the study procedure. After written informed consent of the head of the pharmacy and pharmacy staff, the pharmacies will be assigned to control or intervention group (cluster randomization). There will be exclusive control pharmacies and intervention pharmacies.

Pharmacy staff addresses potential study participants according to the inclusion criteria during daily routine in the community pharmacy. It is possible within the scope of this study to train the use of different dosage forms for the same patient or family caregiver. In order to identify a potential administration error, the pharmacy staff asks the patient or family caregiver to use the medicine (duration approx. 2-5 minutes). Such a demonstration is quite common in the context of the usual pharmaceutical counseling. The demonstration can be performed with the patient's drug itself or with a placebo. The pharmacy staff assesses a possibly incorrect administration by using a checklist defined in advance for a specific dosage form. Checklists and placebo materials are provided by the Department of Clinical Pharmacology and Pharmacoepidemiology. In the control group, pharmacy staff provides a standard consultation (duration approx. 3 minutes) followed by the provision of standardized information material, e.g. written step-by-step

instructions. In the intervention group, the staging algorithm (Fig. 1) is used to determine the individual level of the patient or caregiver according to the Transtheoretical Model. The stage "Maintenance", i.e. the permanent correct use of the drug, cannot be detected with this algorithm. The purpose of this model is to identify in particular those medicines users who are not aware of administration errors despite incorrect use of the drug and who may not be motivated to seek training or detailed counseling.

[figure not shown]

Figure 2. Staging Algorithm

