## **15. Statistical method**

### **Statistical design**

The error rate of the intervention group will be compared to the error rate of the control group by the chi-square test. The error rate of the medication administration before patient education will be compared to the error rate after the training by the McNemar test. A  $p\text{-value} \leq 0.05$  is considered as statistically significant. Feasibility of the education method into the daily routine of the community pharmacy and the contentment of the patients and family caregivers will be analyzed qualitatively. The influence of co-variables like dosage form, patient characteristics, educating person and number of drugs on the education success will be determined by logistic regression.

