**Calculation of sample size based on the primary outcome**

Due to the results of a randomized study which has compared a complex education intervention for the correct application of inhalers with a standard consultation, we presume a difference for the success of the intervention in the control- and intervention groups of 20%, with success rates of  $p_1=32\%$  and  $p_2=52\%$  [22]. To determine a significant difference between the control- and intervention group by the chi-square test (unrelated sample,  $\alpha = 0.05$ ;  $\beta = 0.8$ ), it is required, in due consideration of a drop-out rate of 15% after 6 months, a cluster size of 5 community pharmacies per group and a cluster effect (Intraclass Correlation Coefficient, ICC) of 0.02,  $n=122$  medication administrations of a dosage form e.g. eye drops or transdermal patches per group. With a cluster size of 10 community pharmacies per group the sample size of the dosage form increases to  $n=133$  per group. The calculation of the sample size is carried out on the level of dosage forms because then patients who apply for various dosage forms can be educated according to their individual drugs. The follow-up visit after 12 months will be described qualitatively.

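### The sample size is set for one dosage form, but the primary outcome is one undivided error rate to which a person may contribute several forms; the primary unit and test need fixing and the size recomputing

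*Protocol*

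**What the plan says.** Section 4 of the protocol states the primary outcome as one rate: "Rate of incorrect medication administration will be compared between control and intervention group at 6-month follow-up". No dosage form is named. Section 15, under the statistical design, gives one between-group comparison: "The error rate of the intervention group will be compared to the error rate of the control group by the chi-square test". A p-value of 0.05 or less "is considered as statistically significant", and no rule for several tests is given.

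The sample-size paragraph, which says it is based on the primary outcome, uses a different unit. It asks for 122 administrations of a dosage form per group, with eye drops and transdermal patches as examples, or 133 under the ten-pharmacy alternative, and adds: "The calculation of the sample size is carried out on the level of dosage forms". Section 7 only refers the reader to this paragraph, so it is the sole statement of trial size.

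Section 8 admits five forms: eye drops, transdermal patches, tablets to divide, liquid oral preparations and capsules. Section 11 says: "It is possible within the scope of this study to train the use of different dosage forms for the same patient or family caregiver". The only correlation allowed for is the pharmacy ICC of 0.02, and it enters the size, not the test. Dosage form and number of drugs appear as covariates in a logistic regression of education success (section 15), which serves a secondary outcome in section 4.

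**The concern.** The unit that was sized (one form) is not the unit of the primary outcome (all administrations together), and the protocol does not say which governs the primary comparison. The choice sets the size of the trial: 2 × 122 = 244 to 2 × 133 = 266 administrations in total for one pooled test, against 1,220 to 1,330 if each of five forms is fully sized. A protocol has to settle that itself.

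Each reading has a weakness as written.

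- **Pooled.** A chi-square test on administrations counts two forms used by one person as two independent observations. Someone who makes errors with one form may well do so with another, so the variance is understated. The comparison is also unadjusted for form, although errors are scored on form-specific checklists and the protocol itself asks whether success depends on the form. As few as five pharmacies per group are randomized, and staff approach participants after allocation, so the mix of forms could differ between arms.
- **Per form.** There could be several primary tests at 0.05, with nothing to control the chance of a false positive among them.

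**Working it through.** **Inputs from the protocol (section 15):** success rates of 32% and 52%, stated as a "difference for the success of the intervention in the control- and intervention groups of 20"%; alpha 0.05; power 80% (printed as beta = 0.8); a "drop-out rate of 15% after 6 months"; "a cluster size of 5 community pharmacies per group", or ten; ICC 0.02. Sidedness is not stated; two-sided reproduces the figures.

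**1. Reproducing 122 and 133.** With mean proportion 0.42:

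n = [1.960 × √(2 × 0.42 × 0.58) + 0.842 × √(0.32 × 0.68 + 0.52 × 0.48)]² / 0.20² = 94.4, rounded up to 95 per group.

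- Design effect 1 + (5 − 1) × 0.02 = 1.08: 95 × 1.08 = 102.6, up to 103; 103 / 0.85 = 121.2, up to 122.
- Design effect 1 + (10 − 1) × 0.02 = 1.18: 95 × 1.18 = 112.1, up to 113; 113 / 0.85 = 132.9, up to 133.

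Both match. They are the size for a single two-sided 5% test, with no allowance for several forms or for several administrations per person.

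**2. Pooled reading.** The protocol gives neither the number of forms per person (f) nor the within-person correlation (r). Assume f = 1.2 to 2 and r = 0.1 to 0.6. The extra design effect is D = 1 + (f − 1) × r, and the actual type I error of a nominal 5% test is 2 × [1 − Φ(1.960 / √D)]. The required size is 95 × 1.08 × D (or 95 × 1.18 × D), rounded up, divided by 0.85 and rounded up again.

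| f | r | D | Type I error | Size per group (1.08 / 1.18) | Power at 122 |
|---|---|---|---|---|---|
| 1.2 | 0.1 | 1.02 | 5.2% | 124 / 136 | 80% |
| 1.5 | 0.3 | 1.15 | 6.8% | 139 / 152 | 75% |
| 2 | 0.3 | 1.30 | 8.6% | 158 / 172 | 70% |
| 2 | 0.5 | 1.50 | 11.0% | 182 / 199 | 63% |
| 2 | 0.6 | 1.60 | 12.1% | 195 / 212 | 60% |

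The power column is that of a test that allows for the correlation; at D = 1 it is 81%. These figures isolate the within-person effect and take the protocol's own pharmacy inflation as given. Using the mean f slightly understates D when the number of forms varies. If a quarter of participants bring two forms and the rest one, then f = 1.25, but the term multiplying r is (0.75 × 1 + 0.25 × 4) / 1.25 − 1 = 0.4, not 0.25.

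**3. Form mix.** If two forms differ in error rate by g and the share of one form differs between arms by s, an unadjusted comparison shows a difference of g × s with no training effect. For assumed g of 0.10 to 0.30 and s of 0.10 to 0.20, that is 0.01 to 0.06, or 1 to 6 percentage points, against a planned effect of 20.

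**4. Per-form reading.** The family-wise error for k independent tests is 1 − 0.95^k: 9.75% for two, 14.3% for three, 18.5% for four and 22.6% for five. Bonferroni over five forms (alpha 0.01) needs 141 per group before inflation. Then 141 × 1.08 = 152.3, up to 153, and 153 / 0.85 gives 180; 141 × 1.18 = 166.4, up to 167, and 167 / 0.85 gives 197, per form per group. At the stated 122 or 133, power at alpha 0.01 is about 59%.

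**The case against.** The best defence is that sections 4 and 15 are singular: one rate, one comparison. No sentence announces a primary test for each form, and the regression with dosage form as a covariate implies that forms are combined at least there. A reader might infer from the form-level sizing that five primary tests are planned. The protocol does not say so, and it names forms only as examples. That part of the defence stands, and 22.6% can be no more than an upper bound, reached only if all five forms are tested and the tests are independent.

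A reader might also take the reference to an unrelated sample as a claim that all administrations are mutually independent. Beside the McNemar test for the before-after comparison, it most naturally names the two-group form of the chi-square test. The criticism does not need the stronger reading, because that test treats its observations as independent in any case.

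Nor can it be said that form is ignored altogether, or that the comparison is known to be confounded. The planned regression includes form, and pharmacies are randomized, so an unequal mix is a possibility and not an established bias. What remains is that the regression serves a secondary outcome and leaves the primary comparison unadjusted.

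Finally, the exact model could be left to an SAP, and the low end of the pooled range (5.2%) is negligible. Both points are fair. The unit and the number of primary tests are different: they fix the trial's size, which the protocol itself states.

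**Conclusion.** The mismatch is real and should be corrected. The sample size refers to one dosage form, while the primary outcome and test refer to an undivided rate.

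- **Pooled, as sections 4 and 15 suggest:** the plain chi-square test has a type I error of about 5.2% to 12.1%, depending on assumed values of 1.2 to 2 forms per person and a within-person correlation of 0.1 to 0.6. Nothing in the protocol shows which end applies. The primary comparison is also open to differences in form mix.
- **Per form:** no multiplicity rule exists, and the family-wise error is at most 22.6% for five independent tests.

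It would be tempting to conclude that declaring 122/133 the pooled total settles the matter. It does not. The text ties those numbers to one form, and on the assumptions above a pooled test needs about 124 to 195 per group with the 1.08 inflation, or 136 to 212 with 1.18.

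**What to change.** In sections 4 and 15, state one primary test: the pooled 6-month error rate, intervention against control. Replace the plain chi-square test by a model with dosage form as a fixed factor that accounts for correlation within participant and within pharmacy. Random intercepts are one option; with few forms per person and few pharmacies they may be hard to fit, and an equivalent cluster-robust method would serve. Report form-specific differences as secondary, with confidence intervals.

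Then recompute the size for that test with an explicit within-person allowance, or keep the planned number and restate the power it gives. The recalculation should also revisit the pharmacy inflation: 122 and 133 arise only when the number of pharmacies per group is used as the number of administrations per pharmacy. That is a separate matter, but it feeds the same calculation.

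The cost is revised wording and one new calculation. Checklists are already form-specific and participants already have identification numbers, so no new data are needed. The downside is that form-specific significance claims are given up and the stated power becomes somewhat less favourable, or the target number rises.

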## **1. Summary**

Correct prescription, dispensing and administration of drugs are crucial for safe pharmacotherapy. In hospitals, almost every fifth drug dose is administered erroneously. It is supposed that at home, where patients or family caregivers are responsible for correct drug administration, error rates are even higher. Patient education on correct medication administration increases adherence and safety of administration. When comparing different educational interventions, it became evident that they differ significantly in their effectiveness. Training that addresses the individual needs of the patient is more effective than interventions that provide general information. A previous focus group study with patients, family caregivers, and nurses (ethics vote S-206/2013), which aimed at determining drug administration problems, revealed that many medicine users were unaware of drug administration errors. To address the lack of error awareness, the Transtheoretical Model developed by James D. Prochaska and his colleagues provides a theoretical framework. This model involves five different levels that a person goes through when he intrinsically changes his behavior. Studies to improve compliance show that level-specific measures, according to the Transtheoretical Model, positively influence the outcome of an intervention. Therefore, this prospective randomized controlled study, aims to evaluate standardized patient education in community pharmacies. This study takes into account the possibly lacking error awareness of the patient or family caregiver and feasibility in community pharmacies. Pharmacy staff will be trained on the study procedure, use of study material and correct administration of different dosage forms. Subsequently, pharmacy staff includes patients during their daily routine into the study. In a before and after comparison of the intervention group with the control group and follow-up visits, the effectiveness and sustainability of patient education will be evaluated

[figure not shown]

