##### **Secondary outcomes**

- Rate of incorrect medication administration before and after patient education in the control and intervention group.
- Rate of incorrect medication administration during the course of follow-up visits.
- Influence of the consideration of the individual level according to the Transtheoretical Model [20] on the willingness to participate in a training, i.e. long-term (1, 6 and 12 months) correct drug use.
- Univariate and multivariate analyses to evaluate the influence of covariates such as dosage form, patient characteristics, the training person and the number of medicines on training success.
- Qualitative: feasibility of implementation in community pharmacies, satisfaction of patients and caregivers.

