##### **The following general questions are related to the project:**

- Is it possible to motivate patients or family caregivers to attend training by raising awareness of a drug administration error?
- Is the consideration of the individual awareness of the error an advantage in the training compared to a "normal" counseling?
- Is the training success sustainable?
- Is the patient education intervention feasible in the community pharmacy setting?
- Are any differences in training success depending on the dosage form or person?

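### The 12-month administration outcome is reduced to qualitative description although correct use at 12 months is a listed secondary outcome, and McNemar cannot supply the before/after comparison of arms promised in the Summary

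*Protocol*

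**What the plan says.** - **Primary outcome (Protocol, section 4).** "Rate of incorrect medication administration will be compared between control and intervention group at 6-month follow-up".
- **Secondary outcomes (section 4).** These include "Rate of incorrect medication administration before and after patient education in the control and intervention group" and "Rate of incorrect medication administration during the course of follow-up visits". A third item refers to long-term correct use and names 1, 6 and 12 months.
- **General questions (section 4).** One of them is "Is the training success sustainable".
- **Summary (section 1).** Effectiveness and sustainability are to be evaluated as follows: "In a before and after comparison of the intervention group with the control group and follow-up visits".
- **Study procedure (section 11).** Use is demonstrated again at each follow-up visit and scored with the checklist. Users who are in error at a visit are retrained.
- **Statistical design (section 15).** "The error rate of the intervention group will be compared to the error rate of the control group by the chi-square test". No time point is attached. Then: "The error rate of the medication administration before patient education will be compared to the error rate after the training by the McNemar test". No arm is named. Qualitative analysis is assigned to feasibility and satisfaction. A logistic regression addresses covariates of education success, and study arm is not among the covariates it lists.
- **Sample-size paragraph (section 15).** It ends: "The follow-up visit after 12 months will be described qualitatively".

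**The concern.** There are two separate difficulties.

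First, section 15 treats the 12-month visit differently from the way section 4 defines it. The visit yields a checklist result, correct or incorrect, of the same kind as the 6-month primary outcome. Describing it only qualitatively gives up the trial's longest observation of whether correct use persists, and leaves one time point of a listed secondary outcome without an estimate.

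Second, the Summary describes a before/after comparison of intervention with control, but the one before/after method named is a paired test. A reader of the results could be left with one p-value per arm. Two significant results would not show that individualised education beats standard counselling. One significant and one non-significant result would not show it either.

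**Working it through.** **1. The 12-month visit.** Section 4 counts 12 months among the time points for correct use. Section 11 provides a scored demonstration there. Section 15 withdraws quantitative analysis from that visit only, and elsewhere keeps qualitative methods for feasibility and satisfaction. This is a stated rule that conflicts with a stated outcome, so it is more than missing detail.

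**2. What McNemar tests.** Let b be the number of administrations going from incorrect to correct, and c the number going from correct to incorrect. The statistic is (b − c)² / (b + c). It uses only the discordant pairs in one set of pairs, and arm does not enter. Run in each arm, it gives two separate tests of change; run on pooled data, it gives one test of overall change. Neither estimates the difference in change between arms.

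**3. Does sample size rule out a 12-month estimate?** Inputs from section 15: success 32% and 52%, α 0.05 (two-sided assumed), power 0.80 (printed as β = 0.8), ICC 0.02, 15% drop-out at 6 months, and 122 administrations per group with 5 pharmacies or 133 with 10.

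The plan's own figures first:
- n = [1.96·√(2·0.42·0.58) + 0.8416·√(0.32·0.68 + 0.52·0.48)]² / 0.20² = (1.368 + 0.575)² / 0.04 ≈ 94.4, so 95 per group.
- 95 × (1 + 4·0.02) / 0.85 = 120.7, so 121 (printed 122).
- 95 × (1 + 9·0.02) / 0.85 = 131.9, so 132 (printed 133).

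Both agree to within one. They do so with 5 and 10 entered as administrations per pharmacy. For the interval below I use 5 and 10 as pharmacies per group, as the text reads.

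Precision at 12 months, where no loss is stated and 15–40% is my assumption:
- n = N × (1 − loss), m = n / pharmacies per group, DE = 1 + (m − 1)·0.02
- half-width = 1.96·√(0.4672·DE / n), where 0.4672 = 0.32·0.68 + 0.52·0.48

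| N, pharmacies per group | Loss | n | DE | Half-width (points) |
|---|---|---|---|---|
| 133, 10 | 15% | 113.05 | 1.206 | 13.8 |
| 133, 10 | 40% | 79.8 | 1.140 | 16.0 |
| 122, 5 | 15% | 103.7 | 1.395 | 15.5 |
| 122, 5 | 40% | 73.2 | 1.273 | 17.7 |

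With the plan's own design effects (1.08 and 1.18) the range is 13.7 to 16.3 points. With so few pharmacies a t quantile is more cautious. On 18 df (2.101) the 10-pharmacy rows become 14.8 to 17.2, and on 8 df (2.306) the 5-pharmacy rows become 18.3 to 20.8. The interval is wide but worth reporting beside a planned difference of 20 points.

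**4. Denominator of the post-education check.** Section 11 trains intervention users who are in a pre-action stage, and Table 1 defines the action stage as correct use. The second check follows training in the intervention arm and follows the standard instructions in the control arm, where no restriction to users in error is stated. If intervention users who were correct at first are not rechecked, the two post-education rates have different denominators. Illustration, with assumed values: 68% baseline error and half of all errors corrected in each arm. Post-education error is then 50% of those rechecked in the intervention arm and 0.68 × 0.5 = 34% of all control users, a gap of 16 points with no true difference. This reading is an inference; the staging figure is not shown and the text does not say that correct users skip the recheck.

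**The case against.** A reader might infer that sustainability is nowhere compared between arms. The protocol does not support that. The primary outcome compares arms 6 months after education, and the chi-square sentence has no time limit, so it can also cover the post-education and 1-month rates. With randomised arms, a between-arm contrast of post-education error is a legitimate comparison of benefit. That stands, subject to a common denominator and adjustment for clustering.

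A reader might also infer that the secondary outcomes themselves demand a between-arm before/after test. They do not. They ask for rates in both groups and over the visits, and McNemar can serve the first of these as within-arm description. The between-arm wording is in the Summary. That McNemar would be run separately in each arm is itself an inference.

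The 12-month sentence closes a sample-size paragraph, so it may have been meant as descriptive and unpowered. A statistical analysis plan could add detail. Both are possible, but the wording contradicts section 4, and a later document should not have to reverse it.

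Finally, users in error are retrained at follow-up visits. A 12-month contrast therefore does not isolate the durability of the first training. This limits interpretation; it does not argue against reporting the estimate.

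**Conclusion.** The point holds in a limited form. Sections 4 and 15 conflict on the 12-month administration outcome, and the one before/after method named cannot deliver the comparison of arms described in the Summary. Only secondary outcomes are affected; the 6-month primary comparison is untouched.

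The size is what would be lost: a 12-month arm difference with a half-width of about 14 to 18 points. This rests on 15–40% loss (assumed), 32% and 52% success carried over from the 6-month planning values, ICC 0.02 and a normal quantile. A t quantile with 5 pharmacies per group takes the worst case to about 21 points.

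It is tempting to add that McNemar would be significant in both arms whatever the true difference. The protocol gives neither a baseline error rate nor rates of change in either direction, so that claim has no support. The unequal denominators are a risk to be closed by wording, and are not established.

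**What to change.** - **12 months.** For administration errors, replace qualitative description with error rates by arm and the between-arm difference with a cluster-adjusted 95% confidence interval. Label it secondary and make no power claim. Keep qualitative analysis for feasibility and satisfaction.
- **Before/after.** Keep McNemar, if at all, as within-arm description. Name a cluster-adjusted between-arm contrast of post-education error, with its confidence interval, as the before/after comparison.
- **Denominator.** State who is rechecked in each arm and use the same denominator in both, for example administrations incorrect at baseline.
- **Interpretation.** State that 6- and 12-month results reflect the strategy including retraining at earlier visits.

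A longitudinal mixed logistic model with arm-by-visit terms is one way to do this; arm-specific rates and cluster-adjusted differences are enough. The cost is a few sentences and some analysis work. The follow-up data are already scheduled. The one possible addition is a post-education check for any users in the chosen denominator who would otherwise not be rechecked.
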